---

## **PROTOCOL SYNOPSIS:**

Radiation therapy in either the pre- or post-operative setting is a standard-of-care treatment option for patients with soft tissue sarcomas based on randomized level 1 evidence(1). Pre-operative radiation treatment is favored at many institutions over post-operative treatment, most notably because it allows the delivery of a lower dose of radiation to a smaller volume(2). The standard pre-operative radiation dose is 45-50 Gy delivered in 25 treatment sessions over 5 weeks.

The 5-week course of radiotherapy can be challenging for sarcoma patients, many of whom travel great distances to have their care at specialized tertiary sarcoma centers. Logistical hurdles prevent patients from relocating to these tertiary centers for the duration of their radiation treatment. We proposed a shorter, condensed form of hypofractionated preoperative radiation therapy administered over 5 days.

More condensed forms of radiation therapy have been adopted in the treatment of several malignancies as radiation oncologists can more easily spare normal tissues with modern radiation techniques and image guidance(3, 4). There is also a biological rationale for this approach in sarcoma, a tumor that is less sensitive to smaller RT fraction sizes (lower  $\alpha/\beta$  ratio; (5)). The purpose of this study is to investigate the toxicity and disease control outcomes of a 5-day radiation regimen that is biologically equivalent to the standard 45-50 Gy regimen given over 5 weeks (25 treatments).

We recently completed an initial cohort of this study (n=52), which was limited to patients receiving neoadjuvant radiation therapy alone. Initial findings of this study have been reported after over 2.5 years of follow-up, and indicate acceptable rates of short- and medium-term complications, with promising rates of local control, both on par with rates observed using conventional 5-week preoperative radiation(6).

In our initial cohort, we excluded patients receiving neoadjuvant chemotherapy, which is given in patients with highest-risk disease. Currently, patients receiving neoadjuvant chemotherapy receive conventional 5-week preoperative radiation therapy, or in some cases, an abbreviated 8-day course of 28 Gy(7). Now, we propose an expansion cohort to examine our novel 5-day regimen in patients receiving either neoadjuvant RT alone or neoadjuvant RT following neoadjuvant chemotherapy. The goal of this expansion cohort is to compare toxicity outcomes in patients receiving neoadjuvant chemotherapy with patients receiving radiotherapy alone. Should the rate of toxicity be similar in each cohort, then the 5-day approach can become incorporated as a standard-of-care for all patients regardless of the use of neoadjuvant chemotherapy.

**PRIMARY OBJECTIVE (s):**

- In patients undergoing preoperative radiotherapy for extremity or trunk soft tissue sarcoma, compare the major wound complication rate in patients treated with neoadjuvant chemotherapy versus patients receiving neoadjuvant radiotherapy alone.

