**STUDY DESIGN:**

Single arm, non-randomized, phase II trial of preoperative hypofractionated radiation for extremity/trunk soft tissue sarcomas

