**STRATIFICATION:**

Patients will be stratified into two cohorts according to the previous administration of neoadjuvant chemotherapy.

Cohort A: neoadjuvant radiotherapy alone

Cohort B: neoadjuvant chemotherapy and radiotherapy

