#### **INTERVENTION AND MODE OF DELIVERY:**

Hypofractionated radiation will be delivered in the pre-operative setting to patients with soft tissue sarcoma with external beam radiation therapy. Patients in cohort A will receive 6.0 Gy x 5 fractions delivered daily in 5 fractions. Patients in cohort B will receive 5.0 Gy x 5 fractions delivered daily in 5 fractions. Patients will not be treated on weekends or holidays as is standard practice for radiation treatments.

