#### **STATISTICAL METHODS:**

### **1. Analysis of primary end point (major wound complication event).**

1.1 The comparison of major wound complication rates, defined as number of patients with major wound complication events over total number of patients, in cohorts A and B will be assessed using one- sided two-sample proportion test.

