### **3. Analysis of exploratory endpoints**

3.1 The association between these 5 secondary endpoints and potential predictors (tumor size at diagnosis, tumor grade, tumor depth, tumor immune infiltration, patient age, patient sex) will be assessed by Cox proportional hazards model.

3.2 The association between germline mutations and response, toxicity and cancer outcome will be investigated using logistic regression model.

3.3 The impact of radiation on local and systemic immune responses will be evaluated using tumor and blood specimens, and these immunologic changes will be related back to patient outcomes.

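### The primary test is a crude comparison of non-randomised cohorts that, under the Intervention section, also differ in dose, so it compares two treatment packages and shows neither a chemotherapy effect nor the safety of one common 5-day regimen

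*Protocol*

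**What the plan says.** The Study Design entry in the Synopsis reads "Single arm, non-randomized, phase II trial of preoperative hypofractionated radiation for extremity/trunk soft tissue sarcomas". Under Stratification, "Patients will be stratified into two cohorts according to the previous administration of neoadjuvant chemotherapy". The opening Synopsis text describes "neoadjuvant chemotherapy, which is given in patients with highest-risk disease".

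The primary objective is to "compare the major wound complication rate in patients treated with neoadjuvant chemotherapy versus patients receiving neoadjuvant radiotherapy alone". Under Statistical Methods 1.1 the rate is events over patients in each cohort, and the comparison "will be assessed using one- sided two-sample proportion test". The Sample Size Justification repeats that test with a one-sided level of 0.1, 80% power, a 21% rate in cohort A, a 15-point margin and minimum numbers of 123 (A) and 41 (B).

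Statistical Methods 3.1 lists "potential predictors (tumor size at diagnosis, tumor grade, tumor depth, tumor immune infiltration, patient age, patient sex") but uses them only in exploratory Cox models of the five efficacy endpoints. No model is given for wound complications.

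On dose, the Intervention section gives cohort A 6.0 Gy x 5 and states that "Patients in cohort B will receive 5.0 Gy x 5 fractions delivered daily in 5 fractions". The Schema lists both fraction sizes. Section 5.1 prescribes 6 Gy x 5 with no distinction by cohort.

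The Synopsis says that if toxicity proves similar in the two cohorts, the 5-day approach can become standard of care whether or not chemotherapy is used. The Synopsis purpose statement and the first secondary objective describe a single 5-fraction regimen equivalent to 45-50 Gy in conventional fractions.

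**The concern.** Three things change together between the cohorts: chemotherapy, the disease risk that led to chemotherapy and, under the Intervention section, radiation dose. A crude difference in proportions absorbs all three.

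If cohort B has more patients prone to wound complications, non-inferiority can be missed although chemotherapy adds nothing. If it has fewer, or if the lower dose reduces wound complications, a real excess from chemotherapy can be hidden. Either could decide the primary conclusion.

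Even a clean result would concern chemotherapy plus 25 Gy in selected patients against 30 Gy alone in others. That is narrower than what the Synopsis proposes to conclude.

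**Working it through.** **1. Dose contrast.** Inputs: 6.0 Gy x 5 and 5.0 Gy x 5 (Intervention section); alpha/beta of 4 and the comparison schedules 50 Gy in 25 and 28 Gy in 8 (section 2.0); 45 Gy in 25 (Synopsis). Standard linear-quadratic form: BED = n·d·(1 + d/4), and EQD2 = BED / (1 + 2/4) = BED / 1.5.

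| Schedule | BED (Gy) | EQD2 (Gy) |
|---|---|---|
| 50 Gy in 25 | 50 × 1.50 = 75 | 50 |
| 30 Gy in 5 (cohort A) | 30 × 2.50 = 75 | 50 |
| 45 Gy in 25 | 45 × 1.45 = 65.25 | 43.5 |
| 25 Gy in 5 (cohort B) | 25 × 2.25 = 56.25 | 37.5 |
| 28 Gy in 8 | 28 × 1.875 = 52.5 | 35 |

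The plan's own equivalence of 30 Gy in 5 with 50 Gy in 25 reproduces. The cohort B schedule is (50 − 37.5)/50 = 25% below cohort A and also below 45 Gy in 25. It lies near 28 Gy in 8, the schedule to which section 2.0 ties it. The single description as equivalent to 45-50 Gy therefore fits cohort A only.

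**2. What a shift in the crude difference does.** Inputs: 123 and 41 patients, 21% in A, a 15-point margin and a one-sided level of 0.1 (Sample Size Justification). The 205 total reproduces: (123 + 41)/0.8 = 205. The 41/123 split is taken as given; whether it delivers the stated power is a separate matter.

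The plan does not name the form of the test. I use the unpooled Wald limit: declare non-inferiority if (pB − pA) + 1.2816·√[pA(1−pA)/123 + pB(1−pB)/41] < 0.15. The probability is exact, summed over all binomial outcomes.

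The protocol gives no bias size, so the offsets are assumptions. If a factor carries 30% against 12% wound risk and its prevalence differs by 20 points between cohorts, the shift is 0.20 × (0.30 − 0.12) = 0.036. A rounder 5-point shift is shown as well.

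| Situation | Rate seen in B | P(declare non-inferiority) |
|---|---|---|
| True excess 15 points, no shift | 36.0% | 11.3% |
| True excess 15 points, 3.6 hidden | 32.4% | 21.9% |
| True excess 15 points, 5 hidden | 31.0% | 27.3% |
| No true excess, no shift | 21.0% | 76.5% |
| No true excess, 3.6 added | 24.6% | 58.7% |
| No true excess, 5 added | 26.0% | 51.3% |

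**3. Room for adjustment.** Expected events in A: 123 × 0.21 = 25.8. In B: 41 × 0.21 = 8.6 up to 41 × 0.36 = 14.8. The total is about 34 to 41, enough for three or four covariates, but with only about 9 to 15 events in cohort B.

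**4. What adjustment cannot do.** If dose is fixed by cohort, no patient has chemotherapy with 30 Gy or radiotherapy alone with 25 Gy. No regression can then separate dose from chemotherapy; only the wording of the conclusion can deal with that.

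**The case against.** The strongest reply is that the causal target is not the protocol's. The primary objective compares rates in patients who received chemotherapy with those who did not, and whether wound rates are acceptable as treated is a legitimate question. Standardising case mix answers a different one, and could make a high observed rate in cohort B look acceptable. The sample size was built for a two-proportion test, and cohort B will have few events. All of this stands, and it is why the crude test should not be replaced, although a reader might infer that it should.

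A reader might also infer that the cohorts are known to differ in wound risk, or that the bias has a known direction. The protocol speaks of disease risk and nowhere links it to wound complications; lower dose and case mix may pull in opposite directions. The offsets above show sensitivity, not an expected bias.

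A third tempting reading is that the plan commits to giving one regimen to everyone. The sentence is conditional, and the 5-day approach can be read as covering both schedules, each of which has a rationale in section 2.0. The difficulty is milder: the equivalence statements describe one regimen, and the conditional conclusion does not say that the two cohorts' doses differ.

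Finally, complete overlap of dose and cohort rests on the Intervention section. Section 5.1 states only 6 Gy x 5, so that premise is unsettled until the passages agree. An analysis plan not shown may add adjusted analyses, but the protocol itself fixes the primary test as unadjusted.

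**Conclusion.** The concern holds in this form. As written, the primary result compares chemotherapy plus the cohort B dose with the cohort A dose alone, in patients selected differently. It can describe whether wound complication rates are similar as delivered. It cannot attribute a difference, or its absence, to chemotherapy, and it cannot support one regimen equivalent to 45-50 Gy for all patients.

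Modest imbalance would matter: a 3.6-point shift against a 15-point margin roughly doubles false non-inferiority (11% to 22%) or removes about 18 points of power (76% to 59%). These figures rest on assumed offsets, the 41/123 minimum numbers and a Wald limit. The dose part rests on the Intervention section and the protocol's alpha/beta of 4.

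**What to change.** 1. Keep the crude test. Beside it, pre-specify a covariate-standardised risk difference for major wound complications (for example, a logistic model with marginal standardisation), with its one-sided 90% upper limit set against the 15-point margin. Use three or four baseline variables already named in Statistical Methods 3.1, such as tumour size, depth, grade and age. Anatomical site is not on that list and would have to be added if wanted. State that the non-inferiority conclusion is interpreted with both estimates.
2. Reword the Synopsis conclusion and the primary objective so that they concern the cohort regimens as given. State that dose and chemotherapy cannot be separated, and report late morbidity and local control by cohort.
3. Reconcile the Intervention section, the Schema and section 5.1 on the dose by cohort.

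The cost is an amendment to wording and modest programming. The adjusted interval may be somewhat wider, and the model must stay small because cohort B is expected to have only about 9 to 15 events. No extra patients are needed for this change.

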**SECONDARY OBJECTIVE (s):**

- Evaluate the 2 year rate of grade  $\geq 2$  radiation morbidity (subcutaneous fibrosis, joint stiffness, or edema) with a 5 fraction radiation regimen that is biologically equivalent to a standard 45-50 Gy regimen given in 25 fractions.
- Evaluate local control, regional control, distant metastasis, progression free survival, and overall survival.
- Evaluate the functional outcomes as assessed using the musculoskeletal tumor rating scale (MSTS) and the Toronto Extremity Salvage Score (TESS),

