We have now completed our initial analysis of the first 52 patients treated on this 5-day protocol, with encouraging results in terms of local control and toxicity(6). We chose a dose (30 Gy delivered over 5 fractions) that would be biologically equivalent to the conventional radiotherapy dose of 50 Gy delivered over 25 fractions. This was calculated based on the linear quadratic formula, where biological effect (E) is determined by the number of fractions (N) and size of the dose per fraction (d) using the formula  $E = (d + \alpha\beta d^2)Nd$ . The  $\alpha/\beta$  ratio for STS is presumed to be 4. The 5 fraction dose roughly equivalent to 50 Gy administered in 25 fractions is approximately 30 Gy (6 Gy x 5). The 5 fraction dose roughly equivalent to 28 Gy administered in 8 fractions (which is a regimen often used for patients receiving chemotherapy) is approximately 25 Gy (5 Gy x 5).

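### The equivalence to 45-50 Gy in 25 fractions does not fit the 5 Gy x 5 stated for cohort B; the dose statements conflict, and if dose differs by cohort the primary test compares two whole regimens, not the effect of chemotherapy

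*Protocol*

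**What the plan says.** The Secondary Objectives in the synopsis evaluate the two-year rate of grade 2 or worse late morbidity "with a 5 fraction radiation regimen that is biologically equivalent to a standard 45-50 Gy regimen given in 25 fractions". The opening of the Protocol Synopsis describes the purpose of the study in similar terms. Both speak of a single regimen and neither separates the cohorts.

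The synopsis section on intervention and mode of delivery gives two regimens: "Patients in cohort A will receive 6.0 Gy x 5 fractions delivered daily in 5 fractions" and "Patients in cohort B will receive 5.0 Gy x 5 fractions delivered daily in 5 fractions". The Schema also shows both doses.

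Section 2.0 Background matches 30 Gy in 5 fractions to 50 Gy in 25. For the lower dose it uses another reference: "The 5 fraction dose roughly equivalent to 28 Gy administered in 8 fractions" is put at about 25 Gy. It describes that reference as a schedule often used with chemotherapy.

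Section 5.1 prescribes 6 Gy x 5 (30 Gy) to the planning target volume and does not mention cohorts.

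The Primary Objective compares major wound complications in patients who had neoadjuvant chemotherapy with those in patients who had radiotherapy alone. The Protocol Synopsis refers to the 5-day regimen in the singular and says that, if toxicity is similar, "then the 5-day approach can become incorporated as a standard-of-care for all patients regardless of the use of neoadjuvant chemotherapy".

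**The concern.** Two things follow if cohort B receives the dose given in the intervention section.

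First, the equivalence stated in the late-morbidity objective does not describe cohort B. The protocol itself derives that cohort's dose from a different reference schedule.

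Second, every patient with chemotherapy would get 25 Gy and every patient without it 30 Gy. Dose and chemotherapy then coincide completely, and no analysis of these two cohorts can separate them. If a lower dose means fewer wound complications, it could mask toxicity added by chemotherapy and make non-inferiority easier to declare. The Primary Objective and the planned conclusion do not mention the dose difference. A favourable result could therefore be read as showing that chemotherapy adds no wound toxicity to one common 5-day regimen, which the comparison would not have tested.

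**Working it through.** **Inputs.** Section 2.0: "This was calculated based on the linear quadratic formula", and the alpha/beta "ratio for STS is presumed to be 4". Synopsis: "The standard pre-operative radiation dose is 45-50 Gy delivered in 25 treatment sessions over 5 weeks", that is 1.8 to 2.0 Gy per fraction. Cohort regimens: as in the intervention section. Comparator for the lower dose: 28 Gy in 8 fractions (3.5 Gy each), Section 2.0.

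**Formula.** Biologically effective dose BED = N·d·(1 + d/r), with N fractions of d Gy and r = alpha/beta. Equivalent dose in 2 Gy fractions EQD2 = BED/(1 + 2/r). The equation printed in Section 2.0 does not reproduce the protocol's own match of 30 Gy to 50 Gy: with the coefficient read as 4 it gives 4500 against 900, and read as 1/4 it gives 450 against 150. The fault may come from text extraction. The standard form reproduces the match exactly and is used here.

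**Results at r = 4.**

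| Regimen | BED (Gy) | EQD2 (Gy) |
|---|---|---|
| 50 Gy in 25 | 50 x (1 + 2/4) = 75.0 | 50.0 |
| 45 Gy in 25 | 45 x (1 + 1.8/4) = 65.25 | 43.5 |
| 30 Gy in 5 | 30 x (1 + 6/4) = 75.0 | 50.0 |
| 25 Gy in 5 | 25 x (1 + 5/4) = 56.25 | 37.5 |
| 28 Gy in 8 | 28 x (1 + 3.5/4) = 52.5 | 35.0 |

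Both matches in Section 2.0 are reproduced: 30 Gy in 5 equals 50 Gy in 25, and 25 Gy in 5 is 7% above 28 Gy in 8 (56.25/52.5 = 1.071), which fits an approximate match.

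Against the reference in the objective, 25 Gy in 5 falls short by 1 - 56.25/65.25 = 13.8% at the lower end and 1 - 56.25/75 = 25% at the upper end. The 25% is also the gap to cohort A.

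**Sensitivity to alpha/beta.** Values other than 4 are assumptions of this review.

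| r | 25 Gy in 5 vs 45 Gy in 25 | vs 50 Gy in 25 |
|---|---|---|
| 2 | +2.3% | -12.5% |
| 3 | -7.4% | -20% |
| 4 | -13.8% | -25% |
| 6 | -21.7% | -31.2% |
| 10 | -29.4% | -37.5% |

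Equal BED with 45 Gy in 25 requires 25 + 125/r = 45 + 81/r, so r = 44/20 = 2.2. With 50 Gy in 25 it requires 25 + 125/r = 50 + 100/r, so r = 1.0.

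**What confounding could do.** The protocol gives no effect of dose on wound complications, so the offsets below are assumptions. Take the figures in the Sample Size Justification: 21% in cohort A, a 15-point margin, one-sided level 0.1, and 123 and 41 patients. Suppose chemotherapy alone raised the rate by the full margin, to 36%, and the lower dose took some of that away. With unpooled variance, the chance of declaring non-inferiority is Φ((0.15 - (pB - 0.21))/SE - 1.2816), where SE² = 0.21 x 0.79/123 + pB(1 - pB)/41.

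| Assumed dose offset | pB | Chance of declaring non-inferiority |
|---|---|---|
| none | 36% | 10% |
| 5 points | 31% | 25% |
| 10 points | 26% | 50% |
| 15 points | 21% | 78% |

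**The case against.** The strongest objection is that the dose difference is itself uncertain. Section 5.1 prescribes 30 Gy without distinction. If that governs, the dose confounding disappears and the equivalence wording fits both cohorts, but the intervention section, the Schema and the 25 Gy derivation in Section 2.0 are then wrong. This stands, and it is why reconciliation comes first.

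Next, the comparison can be read as one of treatment packages. The Sample Size Justification and the Schema set cohort B against cohort A, the two doses are disclosed, and the planned conclusion speaks of a 5-day approach, which need not mean one dose. The design is openly non-randomised and chemotherapy goes to the highest-risk patients, so an isolated chemotherapy effect was never on offer. This also stands: a package-level conclusion is possible. What remains is that the Primary Objective and the singular regimen in the synopsis leave the dose difference unmentioned.

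Third, a reader might infer that the secondary endpoints will be pooled over two doses. The protocol does not say so. Patients are stratified by cohort, Section 10.1 is silent on pooling, and table layout may sit in an analysis plan that is not shown. Only the late-morbidity objective carries the equivalence wording; the other secondary objectives and Section 1.2.1 do not.

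Finally, the alpha/beta of 4 is stated for the tumour, while the objective concerns normal-tissue morbidity, for which the protocol gives no value. A claim that 25 Gy in 5 falls short at every alpha/beta would be wrong: at an assumed value of 2 it slightly exceeds 45 Gy in 25.

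**Conclusion.** The point holds as a contradiction within the protocol and a limit on what the primary test can show. At the protocol's alpha/beta of 4 and with the standard linear-quadratic form, the 5 Gy x 5 stated for cohort B lies 13.8% to 25% below the reference in the late-morbidity objective, and it reaches the lower end only at an alpha/beta of about 2.2 or less. The Protocol Synopsis, Secondary Objectives, intervention section, Schema, Section 2.0 and Section 5.1 cannot all be right about cohort B.

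If the doses differ as the intervention section says, the primary test can establish only that chemotherapy plus cohort B's stated dose is, or is not, non-inferior on wound complications to cohort A's regimen. It cannot show that chemotherapy adds no toxicity to the same 5-day regimen.

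Two stronger readings are not supported. The protocol does not show that the primary comparison fails, because the package-level question can still be answered. Nor does it show that either dose is the wrong one. The size of any bias is unknown; the probabilities above only illustrate its direction if a lower dose reduces wound complications.

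**What to change.** 1. Reconcile the statements on cohort B's dose in the Protocol Synopsis, Secondary Objectives, intervention section, Schema, Section 2.0 and Section 5.1.
2. Make the equivalence statement in the Protocol Synopsis and the Secondary Objectives cohort-specific, consistent with the reconciled doses and with the matches in Section 2.0.
3. If the doses differ by cohort, word the Primary Objective and the planned conclusion as a comparison of two regimens, state the dose difference there, and do not attribute the result to chemotherapy alone.
4. In that case, also report two-year grade 2 or worse morbidity and local control by cohort as the main result.

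This needs no additional patients or procedures: it is a change of wording plus by-cohort tables. The price is a narrower claim and wider intervals for cohort B, whose minimum is 41 patients.
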